### Risk/benefit assessment: We expect that the activities in this study place subjects at a minimal level of risk, which is consistent across the treatment arms, as the intervention activities are not outside the range of normal hand hygiene activity and do not present a risk great than that encountered in daily life.

1. Physical risk: Mild risk of development of dermatitis, no greater than the risk of frequent (but within normal) handwashing in daily life or work.
2. Psychological risk: None expected (Subjects who self identify as having mental health issues related to hygiene activities will be excluded from the study)
3. Social risk: Subjects may find that the time required to pick up new handwashing materials each day poses a burden
4. Economic risk: None expected
5. Benefit of participating in the study: We don’t expect participants to experience a direct benefit from this study. However the results of this study are expected to benefit anyone, healthcare workers and otherwise, who wash their hands frequently by providing evidence of the methods least likely to cause problems for hand health. More broadly, we expect the health care and humanitarian community to benefit from the recommendations resulting from this and subsequent studies that will provide evidence about which methods are most likely to provide adequate disinfection while also keeping the natural protection of the skin barrier intact.

### Specific methods and techniques used throughout the study: Data will be collected using surveys to assess subject history at baseline, survey to collect information on compliance and hand perception and hand exams throughout the intervention, and patch testing at baseline and endline assessments. All methods are non-therapeutic and carried out for research purposes only.

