*Baseline Assessment and Exclusion Criteria*: At baseline, subjects will 1) respond to a questionnaire (Appendix D), 2) have to a hand exam (Appendix E) and 3) have a patch test applied to test for allergy to any of the study substances (Appendix F). This baseline data will also be used to confirm that subjects do not meet any of the study’s exclusion criteria. The questionnaire will include demographic and contact information, information about personal history of dermatitis and atopic disposition (history of seasonal allergies, asthma, childhood eczema, and hay fever), and typical handwashing behavior. The hand exam will look for signs of current dermatitis or baseline skin abnormalities and assess a score from 0-360 using the Hand Eczema Severity Index (HECSI)16. The patch testing kit (8mm Finn Chambers® on Scanpor® Tape) will be applied using dilutions of all six substances included in the study (soap, hand sanitizer, NaDCC, HTH, stabilized NaOCl, unstabilized NaOCl) in two locations - on the upper back to comply with the gold standard of testing and on the arm to allow for ease of viewing and reporting by subjects.

Subjects will be instructed on how to remove the patches and mark the area tested with a surgical marker 48 hours after application. Subjects will take photos of the patch site and provide the photos to researchers via email, and will also be instructed to notify the study team if they observe any redness inside the target areas. Subjects will also be given the option to report in person to have a photo of the area taken if they are unable to take a photo or uncomfortable emailing the photo to researchers. Subjects will repeat the observation and provide another photo on the 96-hour mark. On Day 7 after application subjects will be seen in person by research staff, who will verify negative patch testing and refer any suspected positive cases to [name], co-PI on the study, for verification.

Subjects who are pregnant or trying to become pregnant and those with a history of dermatitis, any baseline skin abnormalities upon exam, a positive patch test to any study substance, or who are employed in a profession in which hands are regularly exposed to irritants (e.g. healthcare workers, mechanics, hairdressers/cosmetologists, bartenders or dishwashers) and those with a self-reported history of mental health issues that may be triggered by a study related to hygiene will be excluded from the study.

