*Endline*: Endline data collection will occur on the last day of the intervention. All subjects will respond to the daily questionnaire and receive a hand exam as usual, and patch testing will be applied a second time according to the same protocol used during baseline. As during the previous assessment, subjects will remove the patch, mark the area, and take pictures after 48 and 96 hours and the area will be examined in person by a researcher on Day 7. Any suspected positive cases will be referred to [name] for verification and subjects with a confirmed positive will be recommended to avoid the substance in the future.

*Data Analysis*: As a preliminary study, the analysis for this study will be descriptive and foundational for further studies examining substances that show promise. The primary outcome of this study is the development of dermatitis, as measured by both HECSI score and self-perception index where subjects are asked to describe symptoms and discomfort experienced on a scale from 1-10. The HECSI score is a highly sensitive tool designed for use in research and epidemiological studies, and will serve as the gold standard of measurement for clinical dermatitis. However perception and discomfort are highly important aspects of the impact of dermatitis on patients, meaning the self-perception index adds an important dimension to the measurement of dermatitis as an outcome. We plan to compare the proportion of subjects presenting with signs and symptoms of dermatitis in each treatment group, and to stratify the results by gender and history of atopy in order to control for potential confounders.

[figure not shown]

*Figure 2. Study Timeline*

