### Sample size and statistical analysis(es) :

### We plan to enroll 108 total subjects in the study, with 18 randomized to each arm. We will target this number with the understanding that minor attrition may occur, and estimate that we need 15 subjects per arm to complete the study to achieve our goals.

**Randomization Methods**: Randomization will be done after patch-testing results are read, to ensure that no subjects meeting exclusion criteria are involved in the study intervention. A researcher who does not interact directly with subjects will perform randomization. Subjects will be numbered (1-108). 18 subjects will be assigned to each group. A random number generated will be used to generate 18 numbers between 1 and 108. These subjects will be assigned to the first intervention group. Random number generation will be repeated in this way five times, with subjects corresponding to the number assigned to the treatment group for the round. The 18 remaining subjects will be assigned to the last treatment group.

**Blinding**: Researchers assessing HECSI scores for the hand exam and applying and interpreting results of the patch testing will be blinded to subject treatment group. Daily surveys will not record treatment arm and subjects will be instructed not to identify their group to examiners.

It is not possible to blind subjects to treatment, because the difference between soap and water, hand sanitizer, and chlorine solutions are obvious and cannot be obscured. However subjects assigned to one of the chlorine solution treatment groups will not be told which solution they have been assigned.

**Sample Size Calculations:** Because there are no previous handwashing studies using chlorine, soap, or hand sanitizer for handwashing that can provide information on the number of subjects likely to develop dermatitis we are unable to calculate a meaningful sample size for statistical significance. We feel that this small sample size is appropriate for a first study. For example if 20-100% of participants in a given arm develop dermatitis that will suggest that the method is problematic and should not be recommended, but if 0% of participants develop dermatitis this will be good evidence that the method has potential and should be studied further. This study is intended to be a first investigation that can provide information that could be used in the future for sample size calculations for a larger trial if any of the handwashing materials show potential.

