### Subject Timeline: Subjects will be enrolled during a four week recruitment period during which informed consent will be collected. Subjects will be enrolled in the study for 7 weeks total, 4 of which will consist of daily intervention.

*Week 1*: Subjects will respond to the baseline survey, receive a hand exam, and have the baseline patch testing kit applied. After 48 hours, they will remove the patch and take a photo of the area. Subjects will take another photo after 96 hours and will be instructed to report any redness, bumps, or scaling at the patch site.

*Week 2*: On day 7 after patch testing subjects will receive an in-person examination of the patch test area. Any subjects meeting the exclusion criteria on the basis of the baseline survey, hand exam, or patch testing data will be excluded from the sample. After any subjects meeting exclusion criteria are removed from the sample, subjects will be randomized into one of the six treatment groups.

*Week 3 (Intervention Week 1)*: Week 3 is the first week of the intervention. Subjects will receive an orientation in handwashing procedures for their assigned treatment group and will wash their hands 10x daily with the substance assigned to their treatment group. Subjects will report daily to pick up handwashing materials for the next day and answer a short survey about compliance and hand feel, including a hand exam and photos of hands.

*Week 4 (Intervention Week 2)*: Week 4 is the second week of the intervention. Subjects will wash their hands 10x daily with the substance assigned to their treatment group, and will report daily to pick up handwashing materials for the next day and answer a short survey about compliance and hand feel, including a hand exam and photos of hands.

*Week 5 (Intervention Week 3)*: Week 5 is the third week of the intervention. Subjects will wash their hands 10x daily with the substance assigned to their treatment group, and will report daily to pick up handwashing materials for the next day and answer a short survey about compliance and hand feel, including a hand exam and photos of hands.

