Contact information including phone number and email address will be collected for each patient, and patients will be notified of any changes in the study in writing either through email or in person. These written records of changes will be archived and a description of changes included in any write up of study methods.

1. **Payment, including a prorated plan for payment**: Subjects will receive a total of $600 after successful completion of all study activities. Subjects will receive $100 for each round of patch testing is completed, and $100 for each week of the intervention completed. Although this study presents minimal risk to subjects, a high level of compensation is called for due to the study’s labor-intensive nature including consistent attention to details and the high level of compliance to intervention activities and attendance at assessments over the course of 7 weeks and the inconvenience of patch testing procedures. The fees will be paid in three stages: $100 after the baseline assessment, $200 at the midpoint of the intervention, and $300 after the endline assessment.
2. **Payment for a research-related injury**: [name] will examine any subjects showing signs of dermatitis. Over the counter treatment will be provided by the research team if necessary, but subjects will be covered by personal medical insurance for consultations at [name] clinic. If subjects do not have sufficient insurance the study will cover the costs of this consultation. Subjects will be reimbursed up to $100 for transportation to a consultation at [name] office. Subjects will not be financially compensated for any research-related injuries.
3. **Outcome**: We expect low levels of our primary outcome of dermatitis (as measured by visual dermatitis scale assessed by study staff) and secondary outcome of discomfort (as measured by self-perception of hand feel) and any level of dermatitis, including 0%, will provide valuable data. However a high level of compliance is necessary for the success of the study and will be measured by self-report and observation of materials. We define high compliance as >95% completion of study intervention activities, as measured by survey completion, pickup of materials, and self reported handwashing 10x per day.

1. **Tissue banking considerations**: None

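### No pre-washing reading of the 1–10 self-perception index is planned, so discomfort already present cannot be told apart from discomfort that develops

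*Protocol*

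**What the plan says.** **Outcome.** Under Experimental design, Data Analysis, the protocol states: "The primary outcome of this study is the development of dermatitis, as measured by both HECSI score and self-perception index". The index runs from 1 to 10. The analysis is described as follows: "We plan to compare the proportion of subjects presenting with signs and symptoms of dermatitis in each treatment group". No cut-off on the index, change from baseline or new-onset rule is given. The Outcome item under Subject Participation instead lists a "secondary outcome of discomfort (as measured by self-perception of hand feel", and ties the primary outcome to the visual scale scored by staff.

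**Baseline.** Baseline Assessment and Exclusion Criteria lists demographic and contact data, "information about personal history of dermatitis and atopic disposition", and usual handwashing behaviour. Current hand feel is not listed. In the Subject Timeline, Week 1 reads: "Subjects will respond to the baseline survey, receive a hand exam, and have the baseline patch testing kit applied". Week 2 lists an in-person look at the patch site and randomisation, with no survey.

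**During the intervention.** The Intervention paragraph puts self-assessed hand feel in the tablet questionnaire at the daily evening pickup. The timeline starts this in Week 3, the first week of washing. The section on specific methods gives the same split between the surveys: "surveys to assess subject history at baseline, survey to collect information on compliance and hand perception and hand exams throughout the intervention".

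**Reading of results.** Sample Size Calculations gives an example for one arm taken alone: "if 20-100% of participants in a given arm develop dermatitis that will suggest that the method is problematic". It treats 0% as good evidence that a method has potential.

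**The concern.** Development implies a change from a starting state. HECSI has a starting value, scored at baseline. On the text shown, the self-perception index has none.

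The eligibility criteria do not fill the gap. They screen on dermatitis history, patch test, visible abnormality at the hand exam and irritant occupation. Someone whose hands look normal but feel dry or itchy is eligible. If that person reports symptoms in Week 3, nothing planned shows whether they began before or after the first wash.

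This matters most for the single-arm reading, because randomisation does not remove background discomfort from one arm's absolute percentage. The Outcome item expects low levels of both dermatitis and discomfort, which is where a small background weighs most. The statistical analysis plan can set a cut-off or a change score, but it cannot supply a value that was never collected.

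**Working it through.** **1. Is there a pre-washing value?**

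| Measure | Week 1 | Week 2 | Weeks 3–6 |
|---|---|---|---|
| HECSI | Yes | Not listed | Daily |
| Self-perceived hand feel | Not listed | Not listed | Daily |

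The sources are Baseline Assessment and Exclusion Criteria, Intervention, Study Procedures (Hand exam), Specific methods, and Subject Timeline. They agree that hand feel is first asked in the intervention survey. That survey also asks about adherence to washing, so it presupposes that washing has begun.

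**2. The plan's own figures.** Six arms of 18 give 6 × 18 = 108, as stated. Needing 15 completers of 18 allows 1 − 15/18 = 16.7% attrition. No power calculation is given, so there is none to reproduce.

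**3. Single-arm reading (illustration).** Two assumptions are needed, and neither is in the protocol:
- a share *b* of eligible subjects would report symptoms without any study washing;
- the 20% example is applied to self-reported symptoms.

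Take a product that causes no new symptoms, so X ~ Binomial(n, b). Twenty per cent means at least 3 of 15, or at least 4 of 18.

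P(X ≥ 3) = 1 − Σ C(15, k) bᵏ (1 − b)¹⁵⁻ᵏ, summed over k = 0, 1, 2.

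At b = 0.10 this is 1 − (0.206 + 0.343 + 0.267) = 0.184.

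| Assumed b | P(≥ 3/15) | P(≥ 4/18) | P(0/15) | P(0/18) |
|---|---|---|---|---|
| 5% | 3.6% | 1.1% | 46.3% | 39.7% |
| 10% | 18.4% | 9.8% | 20.6% | 15.0% |
| 20% | 60.2% | 49.9% | 3.5% | 1.8% |

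The chance that at least one of six harmless arms reaches 20% is 1 − (1 − P)⁶. With 15 completers it is 19.8%, 70.5% and 99.6%; with 18 it is 6.3%, 46.2% and 98.4%.

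**4. Comparison between arms.** Let q be an arm's true rate of new symptoms, with background independent of treatment. The observed rate is 1 − (1 − b)(1 − q), so the difference between two arms is (1 − b)(q₁ − q₂). For illustrative true rates of 40% and 10%, the 30-point difference becomes 0.90 × 30 = 27 points at b = 10% and 0.80 × 30 = 24 points at b = 20%. The difference shrinks in expectation but does not change direction.

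**5. HECSI.** The baseline exam falls in Week 1 (days 1–7) and washing starts in Week 3 (day 15), a gap of about 8 to 14 days. Visible abnormality at that exam excludes the subject, so only signs arising in that gap could be misattributed.

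**The case against.** **The text may not be exhaustive.** The specific-methods sentence is a summary and is itself incomplete: it omits the baseline hand exam required elsewhere. The questionnaire list says what is included, not that nothing else is, and Appendix D is not shown. This stands as a limit on certainty. Still, the baseline list, the methods summary and the timeline all leave hand feel out, and the text gives no sign that it is asked before washing.

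**No rule counts any discomfort as dermatitis.** Correct. A reader might infer that pre-existing discomfort will be scored as developed dermatitis, but the protocol sets no cut-off and no case rule for the index. What is supportable is that prior and new discomfort cannot be separated.

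**The 20% figure is an example about dermatitis.** Also correct. HECSI is named the gold standard for clinical dermatitis, and the Outcome item makes the index secondary. Read as HECSI-defined dermatitis, the example is untouched by the binomial figures. They apply only if it is carried over to self-reported symptoms, which the Data Analysis definition permits but does not require. The background rate is assumed, and screening, hypoallergenic products and free use of Vaseline may keep it low.

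**Daily records show trajectories.** A stable complaint and a worsening one would look different over four weeks. This helps in part, but a series that starts after washing begins cannot show whether its first level was already there.

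**Randomisation balances prior discomfort.** It does in expectation, which rules out a claim of systematic bias between arms. It does not help the single-arm reading.

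**Conclusion.** The point holds for the self-perception index alone. On the protocol text, no value is planned before washing, symptoms without visible signs do not exclude, and no later analysis can recover the missing value. Each arm's absolute proportion with symptoms would mix prior and new discomfort. Comparisons between arms would be diluted by the factor (1 − b).

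The size cannot be fixed from the documents. Under the two assumptions stated, a harmless arm reaches 20% with probability 3.6% to 60.2% with 15 completers, or 1.1% to 49.9% with 18, for a background of 5% to 20%.

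Two further readings are tempting and not supported. One is that HECSI shares the defect: it has a Week 1 baseline backed by exclusion of visible abnormality, and the short gap before washing is minor. The other is that baseline adjustment would sharpen comparisons of mean scores: the protocol plans descriptive proportions, stratified by gender and atopy, and proposes no comparison of means.

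For a preliminary, descriptive study this is a cheap and worthwhile improvement. It does not invalidate the design.

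**What to change.** First check Appendix D. If it already asks about current hand feel on the same 1–10 scale, say so in the protocol body. If it does not:

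- Administer the hand-feel items of the daily questionnaire once before randomisation, either with the Week 1 baseline survey or at the Day 7 patch-reading visit in Week 2. Both visits are already scheduled, and at both the answer is given without knowledge of the arm. Day 7 is closer to the start of washing.
- State this in Baseline Assessment and Exclusion Criteria, in the specific-methods section and in the Subject Timeline. Eligibility need not change.
- In Data Analysis, report self-perceived outcomes as new or increased symptoms relative to that value. In the same edit, reconcile whether the index is primary (Data Analysis) or secondary (Outcome item).

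**Cost.** One short form per subject: 108 on top of 28 × 108 = 3,024 daily forms, or 108/3,024 = 3.6% more, and slightly more if people later excluded also complete it. There is no extra visit, and the sample size stays at 108.

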### Laboratory tests: None

### Study Procedures:

### *Hand exam*: Subjects will receive a visual inspection of hands assessing a score for the severity of erythema, infiltration/papulation, vesicles, fissures, scaling, and edema at different locations on the hands and the extent of the area affected. This evaluation is used to calculate a HECSI score at baseline, and daily during the intervention using the form in Appendix E. Photos of hands will also be taken daily.

*Patch Testing*: Subjects will have patch testing done at baseline and endline for all the substances included in the study with data and results recorded in the form shown in Appendix F. Each substance used in the study will be diluted and placed on the skin under a patch sealed with hypoallergenic tape (8mm Finn Chambers® on Scanpor® Tape) in two areas – on the back and upper arm. Testing on the back provides the gold standard, and patches on the arm will allow for easy observation and reporting by subjects. 48 hours after application, subjects will be asked to remove the patch, identify the testing area by marking it with a surgical marker, and take a photo of the area to provide to researchers. Subjects will provide another photo 96 hours after application. Subjects will be instructed to contact study staff if they observe any redness or suspect a reaction within one of the six testing areas. 7 days after testing, researchers will visually inspect the patch-testing site. Suspected positives will be referred to [name] for confirmation.

### Subject Timeline: Subjects will be enrolled during a four week recruitment period during which informed consent will be collected. Subjects will be enrolled in the study for 7 weeks total, 4 of which will consist of daily intervention.

*Week 1*: Subjects will respond to the baseline survey, receive a hand exam, and have the baseline patch testing kit applied. After 48 hours, they will remove the patch and take a photo of the area. Subjects will take another photo after 96 hours and will be instructed to report any redness, bumps, or scaling at the patch site.

*Week 2*: On day 7 after patch testing subjects will receive an in-person examination of the patch test area. Any subjects meeting the exclusion criteria on the basis of the baseline survey, hand exam, or patch testing data will be excluded from the sample. After any subjects meeting exclusion criteria are removed from the sample, subjects will be randomized into one of the six treatment groups.

*Week 3 (Intervention Week 1)*: Week 3 is the first week of the intervention. Subjects will receive an orientation in handwashing procedures for their assigned treatment group and will wash their hands 10x daily with the substance assigned to their treatment group. Subjects will report daily to pick up handwashing materials for the next day and answer a short survey about compliance and hand feel, including a hand exam and photos of hands.

*Week 4 (Intervention Week 2)*: Week 4 is the second week of the intervention. Subjects will wash their hands 10x daily with the substance assigned to their treatment group, and will report daily to pick up handwashing materials for the next day and answer a short survey about compliance and hand feel, including a hand exam and photos of hands.

*Week 5 (Intervention Week 3)*: Week 5 is the third week of the intervention. Subjects will wash their hands 10x daily with the substance assigned to their treatment group, and will report daily to pick up handwashing materials for the next day and answer a short survey about compliance and hand feel, including a hand exam and photos of hands.

*Week 6 (Intervention Week 4)*: Week 5 is the fourth and final week of the intervention. Subjects will wash their hands 10x daily with the substance assigned to their treatment group, and will report daily to pick up handwashing materials for the next day and answer a short survey about compliance and hand feel, including a hand exam and photos of hands. At the end of Week 6 subjects will be given the endline assessment, which includes a second round of patch testing.

*Week 7*: At the end of Week 7 subjects will have the results of endline patch testing read on Day 7 after application, concluding their involvement in the study.

[figure not shown]

*Fig 2. Subject Timeline*

1. **Assessment of Subject Safety and Development of a Data and Safety Monitoring Plan**
   - - 1. **Definition of Serious Adverse Event (SAE) and Adverse Event (AE) for this study**:

Serious Adverse Events and Adverse Events will be defined as stated in the Tufts Medical Center/Tufts University Health Sciences IRB’s Unanticipated Problem and Adverse Event Reporting Policy. An adverse event is “any untoward or unfavorable medical occurrence in a human subject, including any abnormal physical exam or laboratory finding, symptom, or disease, temporally associated with a subject’s participation in the research.” Subjects will be seen daily by researchers and receive a hand exam, allowing any problems encountered to be identified immediately. [name] will examine subjects experiencing any adverse symptoms or discomfort and is responsible for determining the severity of the issue and whether the issue is likely related to the research activities. Table 2 provides a framework for response to suspected cases of dermatitis. These ranges and treatment options are guidelines, and actions to be taken are ultimately at the discretion of [name]. Subjects who have a very low level of discomfort may be assessed but not need any treatment. Subjects with more significant symptoms or discomfort may be provided with over the counter treatment or prescription treatment based on [name] assessment. If subjects experience a HECSI score above 270 (out of 360) they will most likely be removed from the study. Subjects are also free to withdraw at any time and [name] may remove subjects at her discretion.

| **Level** | **HECSI Score** | **Consult** | **Treatment** | **Study Implications** |
| --- | --- | --- | --- | --- |
| 1 | 68-134 | Telephone Consult | None | None |
| 2 | 135-202 | Telephone Consult | Over the counter | None |
| 3 | 203-269 | In-person Consult | Prescription | None |
| 4 | 270-360 | In-person Consult | Prescription | Participation terminated |

*Table 2. Response to Suspected Dermatitis*

A Serious Adverse Event (SAE) is defined by the Tufts IRB as: “any AE that: 1) Results in death, or 2) Is life-threatening, or 3) Results in hospitalization or prolongation of existing hospitalization, or 4) Results in a persistent or significant disability/incapacitation, or 5) Results in a congenital anomaly/birth defect, or 6) May jeopardize the subject’s health and may require medical or surgical intervention to prevent one of the other outcomes listed above.” [name] is responsible for determining the severity of the issue and whether the issue is likely related to the research activities. SAEs for this study are unanticipated, and will be treated as an Unanticipated Problem if [name] determines that they may be related to study activities.

This study will not have a Data and Safety Monitoring Board because it is a single site study with minimal risk.

- - - 1. **Reporting timeframe for SAEs and AEs**:

Any AEs that are non-serious but clinically significant will be summarized using the Tufts Summary Report Form and submitted at the end of the study, or at the point of a continuing review if necessary. Unanticipated problems will be reported to the IRB within 5 days if [name] determines that the event is likely related to study participation. If the event appears to be unrelated to study participation, the SAE report will be submitted within 15 business days. [name] is responsible for assessing the severity and relationship to study activities of any adverse events, which will determine which type of reporting is required. Reports and summaries will not contain identifying information about subjects involved.

- - - 1. **Accountability procedures as they relate to drugs, devices, and data:**

*Intervention Materials:*

Chlorine solutions will be made fresh regularly and concentrations will be confirmed using the Hach 8209 sodium thiosulfate digital titration kit. Soap and hand sanitizer will be used within the product expiration dates.

*Data Collection*

Data collection forms will be reviewed on a daily basis for completeness and to quickly identify major errors. [name] will review HECSI scores and photos of hands to identify any subjects that may be in need of follow up. Compliance with the study intervention will be measured by self-report in the daily questionnaire and by observation of the amount of handwashing substance left by each subject on a daily basis.

